**Methods:**

The study protocol takes 2 weeks and is performed from the participant’s home. Measures in week 1 are taken to reflect the CAR and waking under baseline conditions. For the first 3 nights of week 2, participants are exposed to a scent from 30 minutes before awakening until their normal time of awakening to allow the scent to become associated with the CAR. On the final night, participants are forced to wake 4 hours earlier, when cortisol levels are normally low, and either the same (conditioned group) or a different (control group) scent is presented half an hour before this new time. This allows us to test whether cortisol levels are higher after the same scent is presented. The primary outcome is the CAR, assessed by saliva cortisol levels, 0, 15, 30, and 45 minutes after awakening. The secondary outcomes are heart rate variability, actigraphy measures taken during sleep, and self-reported mood after awakening. To perform manipulations and measurements, this study uses wearable devices, 2 smartphone apps, web-based questionnaires, and a programmed scent device.

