### Participants

Participants are recruited from the local Dutch population and compensated with €100 (US $110.25) for participation. Flyers displaying a summary of the study inclusion criteria and procedures as well as the compensation amount are disseminated on social media through word of mouth by students and teachers, in university buildings, and in local student housing. Owing to the novel and exploratory nature of the study design, no sufficiently similar studies are available to form the basis of a power analysis. Studies on similar topics have used different outcome measures and statistical analyses and thus do not offer a usable comparison. Therefore, it was decided to run a pilot study and include as many participants as possible within the grant-permitted timeframe, which resulted in 50 inclusions and 42 participants completing the full protocol. It should be noted that the most similar studies available use a comparable number of participants [24,25,37].

To avoid confounding in the measurement of the CAR by menstrual cycle or age [38], only male individuals between the ages of 21 and 34 years are included, and participants are excluded if their answers during screening indicate obesity (defined as BMI >30 kg/m^2^), brain damage, or HPA axis–related endocrine disorders (Cushing disease or Addison disease). Participants currently taking medication (including glucocorticoid medication) or who have a habit of heavy drinking or recreational drug use are also excluded. Participants are screened for severe somatic or psychiatric conditions that would interfere with the study protocol using the Mini-International Neuropsychiatric Interview Plus (MINI-Plus) [39]. To ensure a regular sleep pattern, participants are screened using the Pittsburgh Sleep Quality Index (PSQI) [40] and excluded if they experience jetlag or participate in shift work up to 1 week before participation. To ensure that participants are able to properly detect the scents used in the study, they are excluded if they indicate that they have olfactory impairments. Participants are also excluded if they report allergies or sensitivity to perfume or similar substances that might indicate an adverse reaction to the scents used in the study or if they show an allergic reaction to the scents in the course of the study.

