### Statistical Analysis

The data will be checked for outliers and all relevant assumptions. If cortisol values deviate strongly from normality, a log transformation will be performed. An α level of .05 will be used for all analyses, and an effect size (Cohen *d* or partial eta squared, as appropriate) will be calculated for all effects.

Sensitivity analyses will be performed to investigate the effect of including participants who do not show a CAR in week 1 (defined as an increase of at least 2.5 nmol/L above baseline [8]) and the effect of including participants with incomplete data.

A conditioned effect on cortisol values can be defined in 2 ways: by a higher increase in the CAR from baseline (first week) to evocation (second week) for the experimental group (same scent on evocation) than the control group (different scent on evocation), and by a higher increase in the initial cortisol value (first measure of the CAR) from baseline (first week) to evocation (second week) in the experimental group than in the control group. Therefore, 2 separate analyses will be performed. For the first definition, cortisol levels over each day will be transformed into a single score by computing the area under the curve with respect to the first value (area under the curve with respect to increase [7]). We will then perform a linear mixed-model analysis with week (baseline vs evocation) and group (experimental vs control) as fixed factors. For the second definition, we will again perform a linear mixed-model analysis, replacing the area under the curve with respect to increase value with the first cortisol value after awakening. To check for confounding variables, sociodemographic and personality variables will be included as random factors in both the analyses.

Linear mixed models are also used to analyze the secondary outcomes. Heart rate variability measures 30 minutes before awakening and 45 minutes after awakening will be analyzed separately. In both cases, week (baseline vs evocation) and group will again be fixed factors. For the secondary psychological outcomes affect, stress, vitality, and fatigue, the measurement time (0 vs 30 minutes after awakening) is added as an additional fixed factor.

Finally, multivariate regression will be used to explore the possible moderating or mediating role of psychological variables (affect, personality, and perceived stress) on the effects of conditioning.

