## Discussion

The design of this study is intended to classically condition the CAR by repeatedly presenting a scent in the half hour immediately before awakening, immediately before the CAR normally occurs. If the conditioning is successful, participants should respond to the CS with higher cortisol levels even when it appears in the middle of the night, when cortisol levels are normally far below the morning levels. The outcomes of this study could offer more insight into learning during sleep, learning influences on physiological processes, and manipulating the diurnal rhythm. These findings may also aid in the treatment of sleep rhythm and cortisol disorders.

This study uses a novel design that combines the finding that conditioning is possible during sleep [24,25] with the idea that the diurnal rhythm itself could be conditioned [31,32]. While other studies have investigated whether cortisol levels are subject to classical conditioning [19,21-23], all of them have used an external UCS to adjust cortisol levels rather than relying on changes brought upon by the natural diurnal rhythm. Even animal studies that relied on less invasive stimuli kept the animals under artificial lighting conditions that are impossible to replicate in daily human life [31,32]. Should the alternative approach of this study be successful in conditioning the CAR, this could indicate that it is not necessary to rely on medication or highly demanding procedures to influence cortisol levels.

Should the conditioning procedure used in this study be successful in affecting subjective wakefulness measures, then a similar conditioning procedure has potential use in the treatment of sleep disorders. The primary target group would likely be those patients who do not respond to or cannot participate in existing behavioral therapies. Pharmacological therapies currently prescribed for this purpose are not always ideal solutions; many, such as benzodiazepines, do more to deregulate than help the sleep cycle and feature unpleasant side effects and risks of dependence [55].

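### The primary cortisol model does not name the week-by-group term that tests its hypothesis, and adjusting the test-night value for week 1 would usually be more precise than the implied change contrast

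*Protocol article*

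**What the plan says.** All of this is in the protocol article.

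- **Hypothesis.** Statistical Analysis defines a conditioned effect in two ways. For the area under the curve with respect to increase, it is shown "by a higher increase in the CAR from baseline (first week) to evocation (second week) for the experimental group" than for the control group. For the first sample, it is shown "by a higher increase in the initial cortisol value (first measure of the CAR) from baseline (first week) to evocation (second week"), again relative to controls. The abstract's Methods paragraph words the question as a test-night comparison: "This allows us to test whether cortisol levels are higher after the same scent is presented".
- **Model.** For the first definition: "We will then perform a linear mixed-model analysis with week (baseline vs evocation) and group (experimental vs control) as fixed factors". The second definition uses the same model with the outcome replaced. Heart rate variability gets the same two factors, and the psychological outcomes gain measurement time as a third. No interaction is named for any of them.
- **Timing.** Under Procedure, week-1 saliva is collected at the regular awakening time and test-night saliva four hours earlier. The Discussion describes that time as one "when cortisol levels are normally far below the morning levels".
- **Treatment contrast.** Under Procedure, both groups follow the same steps until the Thursday visit of week 2, when the control group's cartridge is exchanged.
- **Size.** Participants reports 50 inclusions and 42 completers, and explains that "no sufficiently similar studies are available to form the basis of a power analysis". Statistical Analysis adds: "An α level of .05 will be used for all analyses". The article reports no SD, no correlation between weeks and no expected effect.

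**The concern.** Two linked questions arise.

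First, a between-group difference in change is an interaction. A reader given only week and group as fixed factors cannot tell from the model which coefficient decides the trial and has to infer it from the definitions.

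Second, with two occasions and complete data, the week-by-group coefficient is the difference in mean change scores. Subtracting week 1 in full is efficient only if week 1 predicts the test-night value almost one for one. Here the two values come from different points of the night and from different expected cortisol levels, so a weaker relation is plausible, though the article does not quantify it. Week 1 is a clean pre-treatment covariate because the arms do not diverge until the cartridge exchange. It can therefore be used by adjustment instead of full subtraction.

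Precision is at stake. Recruitment is closed and no power calculation was made, so the choice of contrast is one of the few ways left to gain power.

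**Working it through.** The plan gives no power, effect size or variance, so there is no figure to reproduce.

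**Inputs from the article:** 42 completers; alpha 0.05; two occasions per person.

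**Assumptions:** two-sided test; 1:1 allocation, so 21 completers per arm; test-night SD = 1; week-1 SD = k; correlation between weeks = rho; effect 0.8 test-night SD for illustration. The range shown is rho 0 to 0.9 and k 0.5 to 2.

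**Per-person variances**

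- Change contrast (week-by-group term): 1 + k² − 2·rho·k.
- Test night adjusted for week 1: 1 − rho². For estimating the slope in a small sample, multiply by 1 + 1/(2·21 − 4) = 1 + 1/38 = 1.026.
- Before that factor, the difference is (1 + k² − 2·rho·k) − (1 − rho²) = (k − rho)². It is never negative, and it is zero when rho = k.
- With k = 1 the ratio of adjusted to change variance is (1 − rho²)/(2 − 2·rho) = (1 + rho)/2.
- Subtracting week 1 is noisier than ignoring it when k² − 2·rho·k > 0, that is, when k > 2·rho.

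**Worked example, k = 1, rho = 0.3**

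- Change: variance 2 − 0.6 = 1.40; SE = √(2 × 1.40/21) = 0.365; 0.8/0.365 = 2.19; power 0.57 (noncentral t, 40 df).
- Adjusted: variance 0.91 × 1.026 = 0.934; SE = √(2 × 0.934/21) = 0.298; 0.8/0.298 = 2.68; power 0.74 (39 df).
- SE ratio 0.298/0.365 = 0.82, a fall of 18%.

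**Equal SDs (k = 1), small-sample factor included**

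| rho | Fall in SE | Power, change | Power, adjusted |
|---|---|---|---|
| 0 | 28% | 0.43 | 0.70 |
| 0.3 | 18% | 0.57 | 0.74 |
| 0.5 | 12% | 0.72 | 0.82 |
| 0.7 | 7% | 0.90 | 0.94 |
| 0.9 | 1% | 1.00 | 1.00 |

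**Unequal SDs**

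- k = 1.5, rho = 0.5: variances 1.75 and 0.770; SE falls 34%; power 0.48 to 0.82.
- k = 2, rho = 0.5: variances 3.00 and 0.770; SE falls 49%; power 0.31 to 0.82.
- k = 0.5, rho = 0.5 (so rho = k): variances 0.75 and 0.770; SE rises 1%. For rho from 0.2 to 0.7 at k = 0.5, the SE changes by between +1% and −3%.

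**Simulation.** With 3,000 trials per scenario, both contrasts averaged 0.79 to 0.80 for a true 0.80, and both held about 5% type I error. In one simulated data set, the mixed-model week-by-group coefficient and the difference in mean change were both 0.804, which confirms that they are the same contrast.

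**The case against.** **The interaction is implied.** The article does not say main effects only. It defines the effect as a difference in change and derives the analyses from that definition, and a condensed article need not list every model term. This stands, and it is why the omission is a gap in specification. A reader might go further and infer that the group main effect will be tested. That coefficient averages the untreated week with the test night, so it would estimate half the effect (0.40 for a true 0.80), with power of only 0.25 to 0.43 at equal SDs. The documents do not support that inference, because nothing in the article says the group coefficient is the test.

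**The change contrast is valid.** This also stands. A reader might infer that the different awakening times bias the comparison. They do not: a shift in level common to both groups cancels, and randomisation protects the contrast. The issue is precision.

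**The gain is uncertain.** Correct. The Background calls the response generally consistent within a person, which argues against a very low correlation, although it does not refer to awakening four hours early. A claim of much better precision needs a low correlation or a more variable week 1, and the article establishes neither.

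**Adjustment is not free.** Also correct. It uses one degree of freedom, inflates the variance by about 2.6% at 42 completers and assumes a linear slope. Plain ANCOVA also drops anyone missing either week, which matters when 8 of 50 did not complete. It is therefore not interchangeable with the constrained mixed model when data are incomplete.

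**Conclusion.** The point holds in two parts of different weight. The model statement omits the one term that tests the stated hypothesis. The intended term can be recovered from the definitions, so the article should name it, but this does not show that the wrong test will be run.

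With that term in place, adjusting the test night for week 1 estimates the same effect. Its variance is never above that of the change contrast, apart from the small-sample cost. Under equal SDs, the SE reduction runs from 28% at rho 0 to 1% at rho 0.9. It reaches about half if the week-1 SD is twice the test-night SD, and it is about nil when rho is close to k. These figures rest on assumed values of rho, k and effect size and on 21 completers per arm. Equal SDs are themselves doubtful, given how different the two occasions are.

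**What to change.** For both cortisol definitions, state the primary test as the group difference on the test night, adjusted for the week-1 value of the same outcome. Preferably fit a mixed model with week and week-by-group terms and group means constrained equal in week 1, which keeps participants who lack one week. Use the same form for heart rate variability and for the psychological outcomes, matching week-1 and test-night values at the same measurement time. If the change contrast is kept, at least name the week-by-group term as the test.

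Adding regular awakening time as a covariate is optional and not part of this fix.

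No new data are needed. The statistical cost is the degree of freedom, the small variance inflation and the linear-slope assumption given above. Data collection has closed, the study is preregistered and it is only single-blinded. The change should therefore be dated and recorded before outcomes are compared by group, with the unadjusted week-by-group contrast reported alongside. The article's Results section says that the analysis was not yet complete at publication.

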## Introduction

### Background

The hormone cortisol has far-reaching effects throughout the body, mainly influencing metabolism but also being involved in systems as varied as the immune system [1], memory [2,3], and the sleep-wake cycle [4]. Cortisol is secreted from the adrenal gland as the end product of the hypothalamic-pituitary-adrenal (HPA) axis, a system of cascading secretions that originate in the hypothalamus. Cortisol is perhaps best known for its role in the stress response [5], and thus is often called the “stress hormone” in everyday parlance. However, cortisol does not just fluctuate in response to stress; it also follows several rhythms, including a diurnal rhythm. Cortisol levels are highest in the early morning and decline throughout the day and evening, with levels increasing again in the second half of the night [6]. A visual representation of a typical rhythm is shown in Figure 1. The onset of pulsatile secretion varies, but a strong peak is seen in cortisol increase in the period immediately after awakening in most participants [7]. This peak is referred to as the cortisol awakening response (CAR). The CAR has been extensively studied and has been shown to be generally consistent in size within an individual [7,8] but also influenced by situational variables [9], such as sleep duration in the preceding night [10]. Befitting the role of the stress hormone, the most reliable of the situational variables are stress-related [11]. Reviews of relevant studies suggest that the CAR is partially responsible for preparing the body in anticipation of the events and challenges of the day ahead [9,10]. Anticipation of a stressful and challenging day may lead to an increased CAR [12], while an intervention that reduces stress showed a corresponding decrease in the CAR [13]. Meanwhile, patients with severe amnesia, presumably not expecting anything from the coming day, seem to show no CAR at all [14].

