#### Physiological Measures

##### Cortisol Awakening Response

Participants take saliva measures themselves on 2 consecutive Fridays of the experiment to measure cortisol levels. A total of 4 samples are taken each week: immediately after awakening, 15 minutes after awakening, 30 minutes after awakening, and 45 minutes after awakening. Participants are instructed not to eat, brush their teeth, smoke, exercise, shower, or drink anything other than water between awakening and taking the final sample to avoid any contamination of the samples or confounding of cortisol values [38]. Saliva is collected using sealed swabs designed for cortisol collection (Salivettes; Sarstedt AG and Co). Cortisol is assessed in saliva with a competitive electrochemiluminescence immunoassay using a Modular Analytics E602 immunoanalyzer (Roche Diagnostics). Cortisol activities are measured and expressed in nmol/L. Participants track the times when they take the saliva measures in a smartphone app, using a phone that they receive from an experimenter and use throughout the study to allow the researchers to verify that they were awake and took the required samples at the correct time. Because cortisol samples remain stable at varying temperatures for up to 5 days [41], participants were not required to cool or freeze the samples once collected. Samples were retrieved by a researcher and frozen on the same day they were collected.

The cortisol measure requires participants to be awake, but the scent conditioning procedure operates for half an hour before the participant wakes. To investigate whether the conditioning procedure has an effect before awakening, heart rate variability and actigraphy measures are included that operate throughout the night. These measures also allow for an additional check for whether the participant did indeed awake at the scheduled time.

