#### Questionnaires

All questionnaires used have previously been found to have adequate validity and reliability.

For screening, the participants complete the PSQI [40]. Scores of 5 or higher indicate poor sleep and are used as an exclusion criterion. In addition, participants are screened for mental disorders using the MINI-Plus [39,43] and excluded if they meet the criteria for any disorder.

Several personality characteristics are measured upon inclusion, to check for possible interaction with the main outcome. Specifically, the questionnaires used are the extraversion and neuroticism scales of the Eysenck Personality Questionnaire [44,45] to measure extraversion and neuroticism, the Depression Anxiety Stress Scale-21 (DASS-21 [46]) to measure symptoms of depression and anxiety, the Life Orientation Test–Revised [47] to measure optimism, the Perceived Stress Scale [48] to measure general appraisal of stress, and the Morningness-Eveningness Questionnaire [49] to measure chronotype.

Every day of the study, immediately after awakening or after the first saliva measure, participants complete a web-based diary on their phone or PC, which includes several questionnaires. To measure positive and negative affect, the Positive and Negative Affect Schedule (PANAS [50,51]) is used. Stress is measured using a custom-made Numerical Rating Scale (NRS) asking participants to score themselves between 0 (“not at all”) and 100 (“very much”) on 7 stress-related words [19,52]. Vitality is measured using the Subjective Vitality Scale (SVS [53]), and fatigue using the fatigue subscale of the Checklist Individual Strength (CIS [54]) adjusted to measure the current state of fatigue.

The sleep diary also includes custom-made daily questions about habits that indicate or may influence sleep quality and patterns. Participants are asked about their meal times; their intake of caffeine, alcohol, tobacco, medication, and recreational drugs; sporting activities; the time at which they fell asleep the previous night and the time at which they awoke in the morning; any nighttime awakenings; and their perceived sleep quality.

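### Entering stable participant traits as random factors does not check confounding of the conditioning effect: with both weeks observed, the week-by-group estimate cannot move

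*Protocol article*

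**What the plan says.** Each participant gives cortisol on two days: "Participants take saliva measures themselves on 2 consecutive Fridays of the experiment to measure cortisol levels" (Cortisol Awakening Response). For the first primary analysis, "cortisol levels over each day will be transformed into a single score by computing the area under the curve", so each participant contributes one score per week. The second primary analysis uses the same model, "replacing the area under the curve with respect to increase value with the first cortisol value after awakening".

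The Statistical Analysis section defines a conditioned effect "by a higher increase in the CAR from baseline (first week) to evocation (second week) for the experimental group" than for the control group. It plans a "linear mixed-model analysis with week (baseline vs evocation) and group (experimental vs control) as fixed factors". The week-by-group term is not written out, but this definition implies it.

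The only terms given a random role are the covariates: "To check for confounding variables, sociodemographic and personality variables will be included as random factors in both the analyses". Participant is not named as a random effect. The Questionnaires section says when and why the traits are recorded: "Several personality characteristics are measured upon inclusion, to check for possible interaction with the main outcome". A separate exploratory regression is planned for moderation and mediation.

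Participants are randomised in blocks of 4. Of 50 included, 42 completed the protocol (Participants), and a sensitivity analysis addresses participants with incomplete data.

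**The concern.** A check for confounding has to be able to change the estimate when a prognostic variable is unevenly spread between the groups. Two features of the stated model prevent this.

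- A random factor yields a variance and one shrunken intercept per distinct score. It yields no regression slope, so it does not adjust for a numerical trait such as neuroticism or chronotype.
- The traits are recorded once and are constant across the two weeks, while the effect of interest is a within-person change. A term that shifts both weeks of a participant equally drops out of the change.

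At stake is how the result is interpreted. An estimate that stays the same after the covariates are added could be taken as evidence that imbalance does not matter, when the model could not have shown otherwise. This applies to both primary analyses. With about 21 per group, some chance imbalance is to be expected.

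**Working it through.** The article gives no effect size, standard deviation or power figure, so there is no figure of the plan's own to reproduce. The check is algebra, followed by model fits on simulated data.

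**Algebra for complete pairs.** Let participant *i* have scores y₁ (baseline) and y₂ (evocation), with y = β₀ + β₁·week + β₂·group + β₃·week·group + (any intercepts constant over week) + residual.

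- Difference: y₂ − y₁ = β₁ + β₃·group + residual difference. Every intercept, whether for participant or for a trait score, has cancelled.
- Mean of the two weeks: this is uncorrelated with the difference. Its own intercept and group term are free, so it carries no information on β₃.
- Hence the estimate of β₃ is the group difference in mean change, whichever random intercepts are included.
- A fixed main effect γ·C enters only the mean, so it cancels in the same way.
- A term δ·C·week enters the difference as δ·C. Only then does the estimate adjust for imbalance in C.

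**Simulated check.** Assumed inputs: integer covariate with SD 2; group imbalance 0.8 points (0.8/2 = 0.4 SD); covariate effect 1.5 at baseline plus 0.8 on the week change; participant SD 3; residual SD 2; true interaction 1.0. Estimates of week-by-group (standard error) by REML, 42 complete pairs:

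| Model | Run 1 | Run 2 | Run 3 |
|---|---|---|---|
| Participant intercept | 1.856 (1.047) | 2.763 (1.084) | 0.998 (1.011) |
| plus covariate as random intercept | 1.856 (1.047) | 2.763 (1.084) | 0.998 (1.011) |
| plus covariate as fixed main effect | 1.856 (1.047) | 2.763 (1.084) | 0.998 (1.011) |
| plus fixed covariate and covariate-by-week | 1.568 (0.959) | 1.721 (0.919) | 0.253 (0.925) |
| Covariate random intercept, no participant effect | 1.856 (1.275) | 2.763 (1.425) | 0.998 (1.528) |

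**Incomplete pairs.** Assumed: 50 included, 8 lacking week 2. The article does not say how many of the 8 non-completers lack a second cortisol profile.

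| Model | Run 1 | Run 2 | Run 3 |
|---|---|---|---|
| Participant intercept | 1.119 | 1.899 | 3.239 |
| plus covariate as random intercept | 1.282 | 1.969 | 3.252 |
| plus fixed covariate and covariate-by-week | 0.824 | 1.226 | 2.767 |

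The random intercept does move the estimate here, but in all three runs it moves away from the covariate-by-week estimate. It alters the weight given to participants seen in one week only; the trait's effect on change is still not modelled.

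**How much could go unseen.** The unadjusted part equals the covariate-by-week slope times the imbalance. With an assumed 21 per group (42/2), the standard error of a standardised imbalance is √(1/21 + 1/21) = 0.31 SD. The documents give no slope, so take 0.1, 0.3 and 0.5 SD of the change score per SD of trait as an assumed range. An imbalance of one standard error then shifts the estimate by 0.03, 0.09 and 0.15 SD of the change score. An imbalance of two standard errors (0.62 SD) shifts it by 0.06, 0.19 and 0.31 SD. For comparison, the standard error of the group difference in change is itself 0.31 SD.

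**The case against.** Several counter-arguments carry weight.

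- **The estimate can move.** A reader might infer that the planned terms can never change the estimate. That is too strong. It holds for random intercepts with both weeks observed. It fails with incomplete pairs, and it fails if the covariate is given a random week slope (complete pairs: 1.995, 1.779 and 0.737 in the three runs). The article does not mention slopes, and random factors ordinarily means intercepts, so the narrower statement stands.
- **Random versus fixed is not the whole fault.** This is correct. Changing the covariates to fixed main effects would leave the complete-pair estimate just as it is. The missing element is covariate-by-week.
- **Participant clustering.** A reader might infer that the repeated measures are left unmodelled. The article does not support that. A linear mixed model on two weeks per person normally carries a participant intercept, the covariates are said to be included and not to replace it, and a condensed article may leave this to a fuller plan. Participant is unnamed, no more. If it really were omitted and no other random term carried the pairing, the interaction standard error would grow by 1/√(1 − ρ), that is 1.20, 1.41 and 1.83 at assumed ρ of 0.3, 0.5 and 0.7. That makes the test conservative: the real two-sided level would be 0.019, 0.0056 and 0.0003 instead of 0.05.
- **Randomisation.** Allocation is random, so the unadjusted comparison is unbiased in expectation and only chance imbalance is at issue. This stands, and it limits the severity.
- **The exploratory regression.** It addresses whether traits modify or mediate the conditioning effect. That is a different question from whether imbalance in a trait shifts the estimate, so it does not repair the check.

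**Conclusion.** The point holds in a bounded form. The article states a purpose, checking for confounding, and a method that cannot serve it: with both weeks observed, random intercepts for stable traits leave the conditioning estimate exactly unchanged. This equality follows from the design and does not depend on the simulation inputs. The size of the movements with incomplete pairs, with random slopes or with covariate-by-week terms does depend on assumed inputs, and three runs only illustrate them.

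A reader might go further and infer that the trial's conditioning result is biased. The documents do not support that: groups are randomised, and no trait-by-week effect or actual imbalance is reported. Over the assumed range, the undetected shift runs from about a tenth of a standard error (0.03/0.31) to about one standard error (0.31/0.31) of the group difference. The fault lies in a secondary check, and the main comparison survives it. It should be corrected so that an unchanged estimate is not taken as reassurance.

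**What to change.** Replace the sentence on random factors with one of two specifications, fixed before outcomes are analysed by group:

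1. **Two-week mixed model.** Fixed effects: week, group and week-by-group. Random effect: participant intercept. A short, named set of baseline covariates enters as fixed effects, each with its covariate-by-week term.
2. **Baseline-adjusted model.** Regress the evocation-week value on group, the baseline-week value and the same covariates, with one row per participant and no random intercept (it could not be separated from residual error).

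The two serve the same purpose; the first also keeps participants seen in only one week. Candidate covariates already collected at or before the start include age, chronotype, perceived stress and regular awakening time.

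Sleep on the test night should not be used as if it preceded the divergence of the groups. The Background section names preceding sleep as an influence on the awakening response, but the Procedure section places the cartridge switch at the Thursday visit, before that night.

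The cost is wording and a few degrees of freedom. With 42 complete pairs, the comparison of change has 42 − 2 = 40 residual degrees of freedom unadjusted and 37 with three covariate-by-week terms. The baseline-adjusted model with three covariates has 42 − 6 = 36. The list must therefore stay short; entering the full set of personality scales would be unwise. No new data are needed.
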